##### Control group (online booklet)

The patients allocated to the control group will have access to an online booklet containing general information about self-management of chronic pain, including pain education, advice on healthy lifestyle and sleeping habits and promotion of physical activity. They will also receive one phone call at week 4 and motivational text messages once a week during the study period.

### Economic evaluation

The economic evaluation will be conducted from a societal perspective over 12 months (at the 8 week, 6, 9 and 12 months follow-ups). Intervention costs will be determined by the real costs of maintenance and support, monitoring costs, training and project management costs, number and length of telephone calls, and number of text messages sent to participants. Costs associated with preparing the organisation and developing the website and video recordings will be excluded. We will measure costs by the estimate of healthcare utilisation costs (public and private if possible), patients costs, and lost productivity costs (absenteeism) collected using a questionnaire. Costs will be measured based on the participants’ reported use of the resources using a cost diary given to the participants at baseline.

The healthcare utilisation costs incurred due to chronic pain (e.g., medication, visits to health professionals, hospital stay, visits to emergency departments, diagnostic tests) will be valued using the Brazilian standard costs [39]. The patient costs include costs of community services (e.g., gym), out-of-pocket expenses, over-counter medication, and transportation (private car and/or public transport) and will be based on the self-reported costs of participants. Transportation by car will be valued using Brazilian gasoline prices, and public transportation using the reference price of the city of São Paulo. The lost productivity costs will include absenteeism from work (paid and unpaid) and costs from transportation (private car and /or public transport). The costs of absenteeism from work (paid and unpaid work) and will be valued using gender-specific price weights [40]. Transportation by car will be valued using Brazilian gasoline prices, and public transportation using the reference price of the city of São Paulo.

We will perform cost-effectiveness and cost-utility analyses according to the intention-to-treat principles [41]. Differences in costs and effects will be estimated using seemingly unrelated regression analyses. The incremental cost-effectiveness ratios will be calculated by the difference between intervention costs divided by the difference between intervention effects. Bootstrapping techniques will be performed to estimate uncertainty surrounding the cost difference and incremental cost-effectiveness ratios. The cost-effectiveness analysis will be conduct for pain intensity at 12 months after randomisation. The cost-utility analysis will be conducted using the health utility index measured by the SF-6D (derived from the SF-12) to calculate the quality-adjusted life-years (QALY). Two exploratory sensitivity analysis will be performed, one including the total costs of the intervention (including costs with preparing and developing the website and videos) diluted in a 10-year period, considered as the available period of use of the resource. The second sensitivity analysis will be performed considering only patients with more than 75% of adherence to the program.

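### Transportation is listed under both patient costs and lost-productivity costs, so the societal total, summed as written, contains it twice

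*Protocol article*

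**What the plan says.** All of the costing text is in the protocol article, section Economic evaluation.

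- Perspective and horizon: "The economic evaluation will be conducted from a societal perspective over 12 months".
- Besides intervention costs, the cost components are healthcare utilisation, "patients costs, and lost productivity costs (absenteeism) collected using a questionnaire". Here lost productivity is glossed as absenteeism only.
- Data source: participants' "reported use of the resources using a cost diary given to the participants at baseline".
- Patient costs include, besides community services, "out-of-pocket expenses, over-counter medication, and transportation (private car and/or public transport" (the parenthesis closes there).
- Lost-productivity costs are then defined again: "The lost productivity costs will include absenteeism from work (paid and unpaid) and costs from transportation", followed by the same two modes in parentheses.
- Unit prices: "Transportation by car will be valued using Brazilian gasoline prices, and public transportation using the reference price of the city of São Paulo". This sentence appears twice, word for word, once after each listing.
- Use of the total: "The incremental cost-effectiveness ratios will be calculated by the difference between intervention costs divided by the difference between intervention effects". The section plans both a cost-effectiveness analysis (pain intensity at 12 months) and a cost-utility analysis (QALYs).

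**The concern.** A societal total is the sum of its cost categories, and that sum is right only if the categories do not overlap. Here one item, with the same modes and the same prices, sits in two of them. Travel expense is also not a loss of productivity, and the section's own short gloss of that category leaves it out. An analyst who built the total from the category definitions would add transport twice.

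What is at stake is the economic evaluation only. Cost-effectiveness is a stated aim of the trial and one of its hypotheses, and both planned ratios rest on the cost difference. Nothing else planned would expose the error. Bootstrapping resamples the same duplicated totals. The two sensitivity analyses deal with website and video development costs and with participants above 75% adherence, so neither varies how transport enters.

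**Working it through.** **Inputs.** The categories and their contents come from the Economic evaluation section. The article gives no amount for transport, for any other component or for the total, so there is no stated figure to reproduce and the check is algebraic.

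**Side by side.**

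| Place in the section | Lost productivity contains | Transport also in patient costs? |
|---|---|---|
| List of cost components | absenteeism | not itemised there |
| Category definitions | paid and unpaid absenteeism, plus transport | yes, same modes, same prices |

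The two rows disagree on what lost productivity contains. Under the second, the two categories overlap.

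**Total per participant.** Let I = intervention cost, H = healthcare utilisation, P = patient costs other than transport, A = absenteeism, T = transport.

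- As written: C = I + H + (P + T) + (A + T) = I + H + P + A + 2T
- Transport counted once: C* = I + H + P + A + T
- Excess: C − C* = T

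**Incremental cost and ratios.** Let d denote the intervention-minus-control difference in means and E the effect.

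- dC = dC* + dT
- Ratio as written − ratio with transport once = (dC* + dT)/dE − dC*/dE = dT/dE

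This holds for both ratios, with E as pain intensity in one and QALYs in the other. The shift is zero when dT = 0, even though the mean total in each arm is still too high by that arm's mean T.

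**Relative size.** Let s = dT/dC*, transport's share of the correct cost difference (defined when dC* is not zero). The ratio as written is then (1 + s) times the single-count ratio. The document does not give s. The values below are assumptions that only show how the formula behaves; none is an estimate for this trial.

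| s (assumed) | factor 1 + s |
|---|---|
| −0.20 | 0.80 |
| 0 | 1.00 |
| 0.20 | 1.20 |

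A negative s means that the transport difference has the opposite sign to the total difference. The factor can therefore lie on either side of 1, and the document does not say on which.

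**The case against.** **It may be a drafting slip rather than a costing rule.** No summation formula is printed, and all resource use comes from one diary. Nothing says that a recorded trip will be entered under two headings. The absenteeism-only gloss, the valuation sentence repeated verbatim and the stray conjunction in the sentence that values absenteeism all suggest text that was duplicated while being edited. The investigators may add transport once in practice, or may mean different trips in each category. This stands as a limit: the double count follows from applying the text literally and is not shown to have been intended. It does not remove the defect, because the text contradicts itself and gives no rule that prevents the overlap. Nor is it mere condensation for a journal. The article does not leave the rule to another document; it states one, in conflicting form.

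**The effect may be negligible.** This also stands. Only the between-arm difference in transport cost moves the ratios, and it may be close to zero.

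**A reader might infer that the error favours the intervention**, because the Abstract and Background present avoided travel as an advantage of internet-based care. The documents do not support this. The Background makes that comparison with face-to-face care. Here the control is an online booklet with one telephone call and text messages, the intervention is delivered by website, telephone and text message, and assessments are remote in both arms. A transport difference could arise only indirectly, through other care that participants seek, and the article gives neither its sign nor its size.

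**A reader might also infer a second overlap**, between out-of-pocket expenses and healthcare use valued at standard costs. The text does not say that a visit already valued is entered again as a payment. The ordinary reading is expenses not listed elsewhere, and item-level definitions of that kind can properly sit in a fuller costing document.

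**Conclusion.** The point holds as an inconsistency in the costing rule. The Economic evaluation section places transportation in two cost categories, at the same unit prices, against its own absenteeism-only gloss of lost productivity. Summed as written, this overstates each participant's societal cost by T, the incremental cost by dT (which may be positive, negative or zero) and each ratio by dT/dE.

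This rests on two assumptions: that the categories are added as defined, and that both listings refer to the same trips. The text supports this reading but does not state it outright. Size and direction cannot be determined from the document.

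The matter is a correction to the economic evaluation. Pain intensity at 8 weeks, the sample size, the clinical secondary outcomes and the mediation analysis do not depend on it.

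**What to change.** Before costs are analysed:

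1. List transportation once, under patient costs, with its valuation sentence given once.
2. Define lost productivity as paid and unpaid absenteeism only, in line with the section's own gloss.
3. If two kinds of trip really are meant, state instead which trips belong to each category, so that no trip can fall in both.

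It would help to print the sum that forms the societal total, with each component named once.

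The cost is a few sentences in the Economic evaluation section. The diary, the follow-up schedule and the data collected stay as they are. Settling it before the cost data are analysed also ensures that the choice cannot depend on the results.

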### Statistical methods

#### Sample size calculation

We determined that a minimum of 160 individuals (80 per group) would be required to provide the trial with 90% power to detect a between-group difference of 1.5 point in a 0 to 10 Pain Numerical Rating Scale, with an estimated standard deviation of 2.75 points and two-sided alpha level of 0.05. The estimated sample size would also allow for loss to follow up rate of up to 15%.

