### Outcome measures

The primary outcome will be pain intensity at 8 weeks measured using the Pain Numerical Rating Scale [30], a numerical scale where 0 indicates no pain and 10 indicates maximum pain intensity.

The secondary outcomes will be as follows:
Pain intensity at 6 and 12 months follow-ups;Function at all time points, measured with the Patient Specific Functional Scale [30], a self-reported scale specific for the measurement of functionality, where the patient nominates activities relevant to them and rates their ability to perform each activity on a 0 to 10 scale, with 0 representing “unable to perform activity” and 10 represents “able to perform at the same level as before injury or problem”;Health-related quality of life at all time points, measured with the SF-12 [31], a self-reported questionnaire with 12 questions and classification of 8 different dimensions related to quality of life. Higher scores reflect better quality of life;Kinesiophobia at all time points, measured with the Tampa Scale of Kinesiophobia [32], a self-reported questionnaire with 17 items scored on a four point likert agreement scale (“totally disagree” “partially disagree”, “partially agree”, “totally agree”. Three items [4, 8, 12] are reverse scored. Higher scores on Tampa reflect higher kinesiophobia;Global perceived effect at all time points, measured with the Global Perceived Effect Scale [30], a self-reported scale, with scores of − 5 to + 5, where the progression of the patient’s condition will be classified from a certain point in time. Scores of − 5 indicate the condition is vastly worse while scores of + 5 indicates completely recovered.Anxiety and depression at all time points, measured by the Hospital Anxiety and Depression Scale [33], a self-reported scale with 14 items, 7 for depression and 7 for anxiety. Each item is scored on 0 to 3 scale. Higher scores indicate higher depression or anxiety.Pain catastrophisation at all time points, measured with the Pain Catastrophising Scale [34], a self-reported scale with 13 statements, where the patient ranks the affirmations between 0 being “minimal” to 4 “very intense.” The calculation of the final score is based on 3 subdomains of the scale and higher scores represent higher catastrophising.Pain-related attitudes and beliefs at all time points, measured with the Short Form Orebro Musculoskeletal Pain Questionnaire [35], with 10 items related to musculoskeletal pain each scored from 0 to 10 with total score ranging from 0 to 100. Patients with scores between 51 and 100 points are classified as high risk of developing long-term disability.Self-efficacy at all time points, measured with Pain Self-Efficacy Questionnaire [36], a questionnaire with 22 questions classified in three domains, with a score of each domain ranging from 10 to 100. A total score close to 300 indicates a greater sense of self-efficacy.Adverse events measured by recording the number of adverse events during the intervention period.

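### 80 patients per group cover about 10% loss to follow-up at 90% power, not the stated 15%; at 15% loss power is about 88%

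*Protocol article*

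**What the plan says.** The protocol article, under Sample size calculation, states every input:

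- **Size and power:** "We determined that a minimum of 160 individuals (80 per group) would be required to provide the trial with 90% power".
- **Effect:** a "between-group difference of 1.5 point in a 0 to 10 Pain Numerical Rating Scale".
- **Variability:** "an estimated standard deviation of 2.75 points".
- **Significance level:** "two-sided alpha level of 0.05".
- **Attrition:** "The estimated sample size would also allow for loss to follow up rate of up to 15" per cent.

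Under Outcome measures the endpoint is fixed: "The primary outcome will be pain intensity at 8 weeks measured using the Pain Numerical Rating Scale". The Data analysis section plans a linear mixed model with group-by-time terms. The article gives no target number of evaluable patients, no inflation formula, and no baseline-to-outcome correlation or other reduction in variance.

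**The concern.** The natural reading is that 160 patients give 90% power and still do so after losing up to 15% of them. Because all the inputs are stated, this can be checked directly, and 80 per group looks too few for both statements to be true together.

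What is at stake is how the team reads its own attrition. The trial is run entirely remotely, with follow-up by telephone, message or e-mail, so loss is a practical matter. If 12% to 15% of patients were missing at 8 weeks, a team relying on this sentence would believe that 90% power was intact, when under the stated inputs it would not be.

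**Working it through.** **Inputs** (all from Sample size calculation): difference δ = 1.5; SD σ = 2.75; two-sided α = 0.05, so z = 1.960; power 90%, so z = 1.282; 80 per group; loss 15%. The calculation treats the loss as patients missing from an unadjusted two-group comparison at 8 weeks.

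**1. Evaluable patients needed**

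Normal approximation: n = 2 × (1.960 + 1.282)² × (2.75/1.5)² = 2 × 10.507 × 3.361 = 70.6, so 71 per group (142 in total).

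Exact t-test (noncentral t): 71 per group gives 89.75% and 72 gives 90.2%, so 72 per group (144 in total).

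**2. Trying to reproduce 160 with a 15% allowance**

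| Route | Per group | Total |
|---|---|---|
| Exact t, 72/0.85 = 84.7 | 85 | 170 |
| Normal approximation, 71/0.85 = 83.5 | 84 | 168 |
| Incorrect inflation, 72 × 1.15 = 82.8 | 83 | 166 |
| Incorrect inflation, 71 × 1.15 = 81.7 | 82 | 164 |
| One-sided 0.05, 58/0.85 | 69 | 138 |
| 80% power, 53/0.85 | 63 | 126 |

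None of these gives 160. Multiplying by 1.15, which under-inflates, comes closest but still exceeds 80 per group. By contrast, 144/0.90 = 160 exactly, so the stated size matches a 10% allowance. The article does not show how the figure was derived, so this is an observation and not a claim about its origin.

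**3. What 160 delivers**

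After 15% loss: 80 × 0.85 = 68 per group. The standard error of the difference is 2.75 × √(2/68) = 0.4716, and 1.5/0.4716 = 3.18.

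| Evaluable per group | Loss from 80 | Power, exact t | Power, normal |
|---|---|---|---|
| 80 | 0% | 92.9% | 93.2% |
| 72 | 10% | 90.2% | 90.5% |
| 71 | 11.25% | 89.75% | 90.1% |
| 68 | 15% | 88.4% | 88.9% |

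The largest loss that keeps 90% power is 1 − 72/80 = 10% by exact t, or 1 − 71/80 = 11.25% by normal approximation.

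**4. Size of the gap**

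At 15% loss the type II error is 100 − 88.4 = 11.6%, against 10% planned. The difference detectable with 90% power at 68 per group is 1.54 points instead of 1.50. The total is 8 to 10 patients below the 168 to 170 needed, that is 8/168 = 4.8% to 10/170 = 5.9% short.

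**The case against.** **The gap is small.** This stands. It is 1.1 to 1.6 points of power, and an SD of about 2.68 instead of 2.75 would restore 90% at 68 per group, a change well within the uncertainty of a planning SD. The main claim of 90% power is met with no loss and up to about 10% loss. No design choice or conclusion turns on this point. That limits its weight, but the 15% figure remains wrong on the stated inputs.

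**Allowing for loss need not mean keeping 90% power.** On that reading the attrition sentence says little, and the other statement fails instead: 160 would not be the minimum for 90% power, because 144 suffice without loss.

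**The 15% may refer to 12 months, not 8 weeks.** The article does not say when the loss applies. If it is cumulative to 12 months, loss at the primary time point could be lower. No pattern of loss is given that would support this.

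**The planned analysis is a mixed model, not a t-test.** This is the strongest point. A mixed model can use partial data and may gain precision from baseline, so 88.4% is the power of an unadjusted comparison and not of the planned analysis. With baseline adjustment of the analysis-of-covariance type, a correlation between baseline and 8 weeks of about 0.23 would bring 68 per group back to 90%. But the article states no correlation and does not name baseline adjustment. If the group-by-time term is read as a contrast of changes from baseline with free baseline means, the variance factor is 2(1 − r). At 68 per group, power is then 76% at r = 0.3 and only returns to 88.4% at r = 0.5. The model could therefore raise or lower power, and it cannot be used to defend the sentence as written.

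**Conclusion.** The concern holds. Under the protocol's own inputs, 160 patients give 90% power with up to about 10% loss (11.25% by normal approximation). With the stated 15% loss, power is about 88% (88.4% exact t, 88.9% normal). Keeping 90% after 15% loss would take 168 to 170 patients. The loss allowance is overstated by about a third to a half (15/11.25 = 1.33; 15/10 = 1.5), although the effect on power is small and the trial is not seriously underpowered.

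The result rests on an unadjusted two-group comparison at 8 weeks, equal loss in both groups, and lost patients contributing nothing to that comparison. The article states nothing that would replace these assumptions with more favourable ones.

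**What to change.** Replace the attrition sentence with one that matches the inputs. For example: for an unadjusted two-group comparison at 8 weeks, 80 patients per group give about 93% power with no loss to follow-up, 90% with up to 10% loss, and about 88% with 15% loss. This costs one sentence and no extra patients.

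If the team wants to keep both 90% power and a 15% allowance on this basis, the total has to rise to 168 to 170, that is 8 to 10 more patients. Relying on a baseline correlation to rescue the present wording is not advised unless the model, including how it handles baseline pain, and the assumed correlation are both stated.

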#### Data analysis

The normality of the data will be tested by visual inspection of histograms. Baseline characteristics of the participants will be calculated using descriptive statistics. The between-group differences and 95% confidence interval for the post-treatment outcomes at 8 weeks, 6- and 12-months follow-ups will be calculated using Mixed Linear Models using interaction terms of treatment group versus time. An intention-to-treat approach will be used in all statistical analyses.

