### Settings and eligibility criteria

Patients will be recruited from the community in Brazil. We will include patients aged between 18 and 60 years, seeking treatment for any chronic musculoskeletal pain condition. Eligibility criteria are: pain of at least 3 points on a 0 to 10 Pain Numerical Rating Scale, able to read and understand Portuguese and with internet access. Chronic pain will be defined as pain lasting more than 12 weeks [27].

Exclusion criteria are: nerve root compromise, serious pathologies (e.g., fracture, tumor, inflammatory, autoimmune, and infectious diseases), serious cardiovascular and metabolic diseases (e.g., coronary heart disease, cardiac insufficiency, decompensated diabetes), recent orthopaedic surgery (over the last 12 months), scheduled to undergo surgery in the next six months, or pregnancy. Patients will also be excluded if there is any contraindication to exercise. We will pre-screen for physical activity participation at baseline using the Physical Activity Readiness Questionnaire (PAR-Q) Portuguese version [28, 29].

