
We will also assess the patient’s expectancy for improvement at baseline using the Expectancy of Improvement Numerical Scale [37].

The same outcome measures will be used at the baseline assessment, post-intervention (8 weeks), 6 and 12 months after randomisation.

Eligible participants will be randomly allocated to one of the treatment groups through an electronic platform. After baseline screening, patients will receive a login and password to access the study website. When the patient logs on to the website, he/she will be randomly allocated to one of the two study groups. The assessor who will confirm the eligibility will be unaware about patients’ allocation.

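### The primary mixed model is described by its group-by-time terms with no stated adjustment for baseline pain; adding it would improve precision at no cost

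*Protocol article*

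**What the plan says.** Under Outcome measures, the protocol article fixes the endpoint: "The primary outcome will be pain intensity at 8 weeks measured using the Pain Numerical Rating Scale". Baseline pain is available: "The same outcome measures will be used at the baseline assessment, post-intervention (8 weeks), 6 and 12 months after randomisation".

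Under Data analysis, the estimates are described as "The between-group differences and 95% confidence interval for the post-treatment outcomes at 8 weeks, 6- and 12-months follow-ups", and these "will be calculated using Mixed Linear Models using interaction terms of treatment group versus time". The only role that section gives to baseline data is descriptive. It does not list covariates, say whether baseline pain is one of the modelled responses, or say whether the baseline means of the two arms are constrained to be equal.

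Under Sample size calculation, the target is "90% power to detect a between-group difference of 1.5 point", "with an estimated standard deviation of 2.75 points and two-sided alpha level of 0.05". The section says "a minimum of 160 individuals (80 per group) would be required" and that this also allows for up to 15% loss. No baseline correlation enters the calculation.

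**The concern.** Baseline pain is usually the best single predictor of later pain, and here it is collected in everyone before allocation. The analysis section names a specific model but gives this measurement no part in the effect estimate. The wording fits two plain models:

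- **Follow-up values only.** The 8-week contrast is the difference in post-treatment means.
- **Baseline as a repeated time point, with a free group effect.** The 8-week interaction term is the difference in mean change from baseline.

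The reference to differences in post-treatment outcomes leans to the first, the reference to interaction terms to the second. Neither beats a baseline-adjusted estimate, and they can differ materially from each other. What is at stake is the width of the primary confidence interval and the power of the primary comparison, in a trial whose 160 participants leave no spare power at the stated 15% loss.

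**Working it through.** **Inputs from the protocol article.** Difference 1.5; SD 2.75; two-sided alpha 0.05; 80 per arm; loss up to 15%, so 80 × 0.85 = 68 completers per arm.

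**Assumptions, not in the document.** The correlation ρ between baseline and 8-week pain, shown over a range. The 2.75 is the SD of post-treatment scores. Baseline and follow-up SDs are equal (relaxed in step 4).

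**1. The plan's own figure.** Evaluable n per arm = 2 × (2.75/1.5)² × (1.960 + 1.282)² = 70.6, so 71 (72 by the t distribution). With 68 completers per arm, the SE is 2.75 × √(2/68) = 0.47. Power is 88.9% by the normal approximation and 88.4% by the noncentral t. The stated design is therefore close to an unadjusted two-sample comparison that makes no use of baseline, and at 15% loss it sits just under its 90% target.

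**2. Variance of each contrast, relative to the post-treatment comparison.**

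- Post-treatment only: 1
- Change score: 2(1 − ρ)
- Baseline-adjusted: 1 − ρ²

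Since 1 − ρ² never exceeds 1, adjustment is at least as efficient as the post-treatment comparison. Relative to the change score, the ratio is (1 − ρ²)/[2(1 − ρ)] = (1 + ρ)/2, which is below 1 for any ρ below 1. This gives 0.65, 0.75 and 0.85 at ρ = 0.3, 0.5 and 0.7.

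**3. Power at 68 per arm (noncentral t).** The effective SD is 2.75 times the square root of the factor above.

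| ρ (assumed) | Post only | Change score: SD, power | Adjusted: SD, power |
|---|---|---|---|
| 0.3 | 88% | 3.25, 76% | 2.62, 91% |
| 0.4 | 88% | 3.01, 82% | 2.52, 93% |
| 0.5 | 88% | 2.75, 88% | 2.38, 95% |
| 0.6 | 88% | 2.46, 94% | 2.20, 98% |
| 0.7 | 88% | 2.13, 98% | 1.96, 99% |

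The normal approximation gives values up to about one point higher. At ρ = 0.5 the SE falls from 0.47 to 2.38 × √(2/68) = 0.41. Adjustment brings power back to 90% at 15% loss once ρ is about 0.23 or more.

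A simulation of four-visit data at ρ = 0.5 (200 runs, 68 per arm) agreed. The mean model SE was 0.47 for the interaction contrast with baseline among the responses, 0.47 for follow-up values only, and 0.41 for both the baseline-covariate and the constrained-baseline models. All four estimates averaged about −1.51 against a true −1.5.

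**4. Unequal SDs.** Entry requires "pain of at least 3 points on a 0 to 10 Pain Numerical Rating Scale", which may narrow the baseline distribution. With baseline SD s, the change-score SD is √(2.75² + s² − 2ρ × s × 2.75). At ρ = 0.3 and s = 2.25, 2.0 and 1.75 (assumed), change-score power is 83%, 86% and 88%, against 76% at s = 2.75. At ρ = 0.4 and s = 2.0 it is 90%. The change score is worse than the post-treatment comparison only when ρ is below s/(2 × 2.75): 0.50 at s = 2.75, about 0.36 at s = 2.0. The adjusted figures do not depend on s.

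**The case against.** The strongest objection is that non-adjustment is read from silence. The article does not say that group, time and their interaction are the only terms, and it does not exclude a baseline covariate. A baseline-adjusted or constrained-baseline model is itself a mixed model with group-by-time terms, so it fits the stated wording. A condensed article may also leave covariates to an analysis plan that is not shown. This stands as a limit on the wording: the article states no adjustment, and a reader who infers that it rules adjustment out goes further than the text. It does not remove the point, because the article does specify the primary model, and following that specification literally gives a less precise estimate.

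Second, the planned power does not rely on baseline adjustment. The unadjusted comparison delivers about 88–89% at 15% loss, close to target. This also stands: a material shortfall needs both a free-baseline change-score contrast and a low correlation, and the document states neither.

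Third, the 76% figure is fragile. It requires equal SDs, and the entry floor may make the baseline SD smaller, which shrinks the loss. The same floor could also lower ρ, so the net direction is unsettled. If 2.75 is instead the SD of change, the sample size already matches a change-score contrast and the drop disappears. Even then the (1 + ρ)/2 ratio would still favour adjustment under equal SDs.

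Fourth, a reader might infer that chance imbalance in baseline pain biases the unadjusted result. It does not: under randomisation it is random error already reflected in the standard error, and adjustment removes part of it.

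**Conclusion.** The point holds as a free improvement in precision, not as a correction of bias or of an error in the stated power. Relative to a plain post-treatment comparison, adjustment raises power at 68 completers per arm from about 88–89% to about 91%, 95% and 99% at ρ = 0.3, 0.5 and 0.7. Those figures assume that 2.75 is the post-treatment SD.

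The stronger reading, that the primary analysis will have only about 76% power, is not supported. It needs a change-score contrast, ρ near 0.3 and equal SDs together, and none of these is in the document. At ρ = 0.7 the same contrast would have about 98%. What the document does support is that its wording admits contrasts that could differ by about 12 points of power at ρ = 0.3 under equal SDs (88% against 76%), and that neither plain reading beats the adjusted estimate.

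**What to change.** State in the protocol or analysis plan that the 8-week, 6-month and 12-month values are the responses, with group, time, group-by-time, baseline value and baseline-by-time as fixed effects. A constrained longitudinal model with baseline among the responses and a common baseline mean for both arms serves the same purpose. Name the adjusted between-group difference at 8 weeks as the primary estimate, and use the same model for each secondary outcome that has a baseline value.

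The cost is a sentence or two, fixed before outcome data are seen. It needs no new data or participants and keeps the mixed-model framework. The sample size need not be recalculated, since it does not rely on the baseline correlation.
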